### Experimental group

We will perform ventilation adjustments to proceed with the MHM. The patient will be maintained on dorsal decubitus at the bedside at 30°, on assisted ventilation mode, and controlled volume. Vt will be increased by 150% based on ideal tidal volume; square wave V; inspiratory time (Ti) equal to 1.5 s, adjusted to a peak of inspiratory flow (PIF) lower than the peak of expiratory flow (PEF); RR of 14 irpm, reduced in case of auto-PEEP; PEEP 8 cmH_2_O; FIO_2_ minimum of SpO_2_ of at least 94%. These parameters will be preserved for 10 min. The MV alarms will be adjusted to allow the safety of the maneuver; in addition, in case of Ppeak above 40 cmH_2_O or plateau pressure (Pplateau) above 30 cmH_2_O, the maneuver is immediately interrupted and the previous parameters reestablished. The hyperinflation maneuver will not be associated with any other bronchial hygiene maneuver.

After 10 min, the recommendations of the American Association for Respiratory Care [21] (2010) will be applied in the aspiration procedure, suggesting that the patients are ventilated with FIO_2_ at 100% for 30 s before and 60 s after the procedure to avoid hypoxemia. In this study, each patient will be subjected to tracheal aspiration for 15 s for three consecutive times through a closed aspiration system with catheter number 14. Subsequently, the ventilation parameters will be readjusted according to the initial parameters.

### Control group

The CG will be positioned in dorsal decubitus at 30° and will undergo initial ventilatory adjustments and tracheal aspiration, the same procedures performed in the EG 2 h before the start of data collection. Between T1 and T2, they will only be monitored, not going through the MHM. In T3, they will be aspirated as well as EG. They will undergo non-invasive ICC monitoring at the same moments as the EG.

### Safety assessment and adverse effects

The vital signs (heart rate (HR), RR, MAP, and SpO_2_) will be assessed continuously and registered during the assessment stages through a multiparameter monitor Mindray iMEC12, while capnography will be assessed through a monitor and sensor Dräger Vamos®. Criteria for interrupting the intervention are HR < 60 bpm, systolic blood pressure > 180 mmHg, and diastolic blood pressure < 50 mmHg. The ICP assessed in a non-invasive manner will also be monitored during all procedures and 20 min after the end of the collections. The MV alarms will be adjusted to allow to control the airway pressures.

An expert physiotherapist will be present throughout the collection, and in case of hemodynamic and/or neurological instability, as well as an increase in airway pressures above the allowed values, the collection will be suspended, and a physician of the ICU staff will join the procedure.

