### Interventions

After the assessments, the selected patients are randomly allocated into two groups (Fig. 1): experimental group (EG)—composed of individuals who will be subjected to MHM + tracheal aspiration—and control group (CG)—only tracheal aspiration intervention. All individuals will be positioned on dorsal decubitus at the bedside at 30°; MV is adjusted on assisted ventilation mode, controlling volume, tidal volume (Vt) of 6 ml/Kg of predicted weight, positive expiratory-end pressure (PEEP) 8 cmH_2_O, inspired oxygen fraction (FIO_2)_, peripheral oxygen saturation (SpO_2_) of 94%, and respiratory rate (RR) and flow (V) adjusted to maintain ventilation synchrony and gasometric demands. We will use a number 14 closed aspiration system with verified cuff pressure and the occurrence of leaks. All participants will be subjected to tracheal aspiration, and only 2 h later, the data collection is initiated (Fig. 2). During these 2 h, patients will only be monitored and maintained on the initial position; no concomitant procedures or disconnection of MV circuit are conducted. In case it is not possible to maintain such conditions, the collection is suspended and started again at the appropriate moment. According to Robba et al. (2016), PEEP of 8 does not cause effects on ICP [20].

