In scenarios of normality of ICP and ICC, there is a proportion between the peaks, where P1 > P2. However, in situations of abnormality, there is a change in the morphology of the ICP waveform, with an increase in ICP associated with a low ICC, with P2 > P1. For the TPP variable, the higher the value found, the greater the chance of the peak being P2, which also corresponds to a decrease in the ICC [22, 23].

In this study, the evaluations will be carried out in five (T1–T5) moments:T0: start monitoring, the interval between T0 and T1 is intended to ensure patient stabilization for the start of data collection;T1: capture initial patient data;T2: assess whether the MHM protocol had effects on ICC;T3: verify whether aspiration combined with MHM could lead to different effects on outcomes;T4 and T5: check whether there was stabilization of parameters related to ICC and respiratory mechanics.

The moment of evaluation T2 is the most relevant for the primary outcome; as for the secondary outcomes, evaluations from T2 to T5 are the most relevant.

Data will be collected through a monitor and analyzed using the Brain4care Analytics System, considering that at a time interval, the software selects an average of pulses to form the waves.

To capture the data, the ICP assessment sensor will be chosen according to the cranial circumference (S, M, L, XL) considering as protocol the lowest sensor possible with reading, following the manufacturer’s recommendations. Data collection will start after the coupling procedure and confirmation by the assessor of reading compatible with the acceptable ICP curves.

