### Methods in analysis to handle protocol non-adherence and any statistical methods to handle missing data

Data will be analyzed on an intention-to-treat basis to include all participants based on the random allocation regardless of whether the intervention has been received or not. Adherence to intervention or withdrawal, which is recorded by our trained research assistants on a weekly basis, serves as a covariate and will be included in the data analysis.

Missing data will not be imputed for main primary and secondary analyses. As sensitivity analyses, these analyses will be repeated, using multiple imputation with chained equations for missing data.

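### The safety section suspends data collection, not only the maneuver, so T2–T5 may be missing mainly in experimental patients who reacted badly, which can bias the comparison toward no change

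*Protocol article*

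**What the plan says.** All references are to the protocol article.

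- **Safety assessment and adverse effects:** "in case of hemodynamic and/or neurological instability, as well as an increase in airway pressures above the allowed values, the collection will be suspended". The vital-sign limits stand in the same section: "Criteria for interrupting the intervention are HR < 60 bpm, systolic blood pressure > 180 mmHg, and diastolic blood pressure < 50 mmHg". Neurological instability has no numeric definition there. The section also has the non-invasive ICP signal monitored throughout the procedures and for 20 minutes after collection ends.
- **Experimental group:** if peak pressure exceeds 40 cmH2O or plateau pressure exceeds 30 cmH2O, "the maneuver is immediately interrupted and the previous parameters reestablished". Data collection is not mentioned.
- **Interventions and Control group:** between T1 and T2 the experimental arm receives the maneuver, while controls are only observed.
- **Intracranial compliance:** "The moment of evaluation T2 is the most relevant for the primary outcome". The sensor signal is recorded and averaged by minute.
- **Handling of non-adherence and missing data:** "Data will be analyzed on an intention-to-treat basis to include all participants based on the random allocation". Further, "Missing data will not be imputed for main primary and secondary analyses"; the sensitivity analyses repeat the work "using multiple imputation with chained equations for missing data". Adherence or withdrawal enters as a covariate.
- **Interventions**, on the two-hour preparation period: if conditions cannot be held, "the collection is suspended and started again at the appropriate moment".

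**The concern.** The safety rule acts on the collection. The Experimental group rule, for the same pressure event, acts on the maneuver. Neither says what happens to the T2–T5 readings. A suspension during the maneuver comes just before the reading that matters most for the primary outcome, and in that window only one arm is exposed to the maneuver.

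If the readings are then not taken, they are absent by arm and possibly by response. An analysis of observed values compares the controls with those experimental patients who got through the maneuver. Chained-equations imputation in its usual form assumes that the missing values can be predicted from what was observed. Unless the trigger and the pre-stop readings are in the model, it fills the gap from patients who tolerated the maneuver.

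The trial is described as an equivalence trial and expects to show no change in intracranial compliance. Loss of this kind favours that conclusion, and the stated sensitivity analysis might not reveal it.

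**Working it through.** **Stated figure.** The Sample size section gives 60 patients, 30 per arm. It cannot be recomputed forward, because no SD, Cohen's d or equivalence margin is given. Back-solving for two one-sided tests at 0.05 each, 95% power and a true difference of zero gives a margin of √(2/30) × (1.645 + 1.960) = 0.93 SD. This is used below only as an assumed margin. The bias itself does not depend on it.

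**Inputs.** 30 per arm is from the protocol. Everything else is assumed, because the document gives no rates:

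- p = share of the experimental arm whose compliance worsens
- h = their mean worsening in SD
- q = share of these patients whose T2 is lost
- r = share of the other experimental patients whose T2 is lost

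All other patients, including controls, have a mean shift of 0.

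**Formulas.**

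- True shift over all randomised patients = p × h
- Shift among observed patients = p × h × (1 − q) / (1 − p × q − (1 − p) × r)

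**Loss only among those who worsened (r = 0).**

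| p | patients of 30 | h | true shift | observed, q = 1 | observed, q = 0.5 |
|---|---|---|---|---|---|
| 5% | 1.5 | 2 | 0.10 | 0 | 0.10 × 0.5 / 0.975 = 0.051 |
| 10% | 3 | 2 | 0.20 | 0 | 0.20 × 0.5 / 0.95 = 0.105 |
| 20% | 6 | 2 | 0.40 | 0 | 0.40 × 0.5 / 0.90 = 0.222 |

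**Loss unrelated to compliance (q = r).** The denominator becomes 1 − q, and the observed shift is p × h × (1 − q) / (1 − q) = p × h. There is no bias, only fewer patients. Stops that reflect lung mechanics alone would be of this kind.

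**Imputation.** A separate simulation (4,000 trials, T1–T2 correlation 0.8, every worsened patient's T2 removed, imputation from arm and T1) gave these mean estimates for full data, complete cases and imputed data:

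- p = 10%, h = 2: 0.199, 0.001, 0.001
- p = 20%, h = 2: 0.403, 0.001, 0.000

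An imputation model limited to those variables does not recover the shift.

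**Effect on conclusions** (simulation of T2 alone, 4,000 trials per scenario, assumed margin 0.93 SD):

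| p, h | outcome | all T2 kept | half lost | all lost |
|---|---|---|---|---|
| 10%, 2 | equivalence declared | 80% | 89% | 93% |
| 10%, 2 | significant difference at 0.05 | 11% | 6.5% | 5% |
| 20%, 2 | equivalence declared | 55% | 76% | 92% |
| 20%, 2 | significant difference at 0.05 | 26% | 11% | 5% |

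**The case against.** The strongest reply is that loss of T2 is inferred. The sensor is monitored during all procedures and records by the minute, so the minutes before a stop should exist and later ones may. The word collection could simply mean the study session, in which case the two sections govern different things. This stands to the extent that a reader may not conclude that T2 **is** lost. But no section says that monitored values supply T2–T5 after a suspension, and the safety section speaks of monitoring beyond the end of collection, so it treats the two as separate.

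A reader might also infer that the values are missing because of the outcome. The numeric triggers are airway pressure, heart rate and blood pressure, which need not track the P2/P1 ratio; only neurological instability lies close to the endpoint. Exclusion at entry of high peak pressure, acute respiratory distress syndrome and hemodynamic instability should also lower the suspension rate. Both points stand.

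The estimates of zero follow by construction from deleting exactly the worsened patients, and they should not be read as a forecast. The imputation variables are not listed either, so a richer model using pre-stop readings is possible. The adherence covariate does not restore an outcome that was never recorded.

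Finally, one might read suspension as a later restart, as in the Interventions section. That sentence covers only the preparation period. If it did apply here, a repeat session could stand in for the one with the reaction, although a patient might also react again and be recorded.

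**Conclusion.** The point holds as a gap with a predictable direction and an unknown size. As written, T2–T5 may be missing mainly in experimental patients who reacted badly, and the planned analyses can then lean toward no change **to the extent that suspension is linked to worse compliance**. With an assumed 10–20% of the arm worsening by 2 SD, a true 0.20–0.40 SD becomes 0 if all those readings are lost and about 0.11–0.22 SD if half are. Losses unrelated to compliance need not bias the result toward zero.

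The documents do not support the stronger readings that T2 is certainly lost, that any effect would vanish, or that an intention-to-treat analysis is impossible. Some missing outcomes are compatible with analysis by allocation, but it is weakened if they arise selectively in one arm. Severity: should be fixed.

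**What to change.** Leave every clinical stopping criterion as it is. Reconcile the Experimental group and safety sections so that they say the following:

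1. Stopping the procedure does not in itself stop the recording. Where feasible, the sensor already attached and the bedside monitor go on recording.
2. The last minutes before the stop are retained, and the scheduled T2–T5 readings are taken. Both are needed, because a T2 reading at its planned time after an early stop may miss the reaction.
3. These readings are analysed in the randomised arm, and a repeated session does not replace the first.
4. Suspensions are reported by arm with their reasons.
5. Alongside the multiple imputation, and not in its place, a sensitivity analysis gives an unfavourable value to suspended patients without a T2 reading. The worst observed change in P2/P1 is one option.

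The cost is a few sentences in the protocol and one added analysis, with no new equipment. The drawback is that readings after an event are noisier.

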### Outcome measures

Primary outcomes will consist of the alterations in ICC indicated in the morphology analysis of the ICP wave due to the MHM since in critical neurological patients, it is crucial to control the secondary lesion and complications caused by the need for MV. Secondary outcomes will range from respiratory mechanics and hemodynamic stability.

### Primary outcome

#### Intracranial compliance

The ICC of all participant patients will be measured in a non-invasive manner through the sensor in the ICP equipment B4C BcMM-R-2000, acquired through funding by the National Council of Research. The researchers were trained by the B4C company and are prepared for data collection. To proceed with the monitoring, a sensor is installed by the researcher coupled to the scalp using an elastic band, without requiring any prior preparation or trichotomy.

The sensor is coupled through wires to a monitor that generates a curve and real-time display of ICP wave, in addition to recording the data for further analysis, which is enabled by extensometers capturing the intracranial volume expansions, since the cranial bone is not entirely hard. Therefore, the pulses are converted into numerical data forming the ICP curve morphology in real time [22].

The ICP wave morphology has its layout, such as in the case of the arterial pulse wave, with a total of up to five distinct peaks, of which three are proper and frequent: percussion wave (P1), tidal wave (P2), and dichroic wave (P3). P1 wave is the most constant in amplitude and derives from the pulse of large cerebral arteries to the choroid plexus. P2 wave, in turn, originates from the cerebral elastance direct reflecting the “reverberation” of P1 on both the brain and cranium, that is, ICC. Finally, the P3 wave is separated from P2 by the dicrotic notch corresponding to the closure of the cardiac aortic valve [23].

The analysis system checks all collected data and analyzes it using a previously created algorithm. The data collected by this sensor are qualitative, which means that the ICP has no absolute value; however, it is possible to analyze the morphology of this pressure curve by extracting three values: P2/P1 ratio, TTP, and pulse amplitude. For this study, all calculations were performed from the average of pulses within each minute of monitoring after excluding possible artifacts. These averages were used to calculate the amplitudes of the two main peaks in the wave morphology, P2 and P1. The P2/P1 ratio was calculated by dividing the amplitudes of the two peaks and the TTP by the time interval from the beginning of each pulse to the peak [15].

In scenarios of normality of ICP and ICC, there is a proportion between the peaks, where P1 > P2. However, in situations of abnormality, there is a change in the morphology of the ICP waveform, with an increase in ICP associated with a low ICC, with P2 > P1. For the TPP variable, the higher the value found, the greater the chance of the peak being P2, which also corresponds to a decrease in the ICC [22, 23].

In this study, the evaluations will be carried out in five (T1–T5) moments:T0: start monitoring, the interval between T0 and T1 is intended to ensure patient stabilization for the start of data collection;T1: capture initial patient data;T2: assess whether the MHM protocol had effects on ICC;T3: verify whether aspiration combined with MHM could lead to different effects on outcomes;T4 and T5: check whether there was stabilization of parameters related to ICC and respiratory mechanics.

The moment of evaluation T2 is the most relevant for the primary outcome; as for the secondary outcomes, evaluations from T2 to T5 are the most relevant.

Data will be collected through a monitor and analyzed using the Brain4care Analytics System, considering that at a time interval, the software selects an average of pulses to form the waves.

To capture the data, the ICP assessment sensor will be chosen according to the cranial circumference (S, M, L, XL) considering as protocol the lowest sensor possible with reading, following the manufacturer’s recommendations. Data collection will start after the coupling procedure and confirmation by the assessor of reading compatible with the acceptable ICP curves.

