**Methods:**

Sixty patients aged ≥ 18 years, with clinical diagnosis of acute stroke, confirmed by neuroimaging examination, with onset of symptoms within 72 h, under mechanical ventilation through tracheal tube, will participate in this study. Participants will be randomly allocated into 2 groups: experimental group (*n* = 30)—MHM plus tracheal aspiration—and control group (*n* = 30)—tracheal aspiration only. Intracranial compliance will be measured by a non-invasive technique using Brain4care BcMM-R-2000 sensor. This will be the primary outcome. Results will be recorded at 5 times: T0 (start of monitoring), T1 (moment before MHM), T2 (moment after the MHM and before tracheal aspiration), T3 (moment after tracheal aspiration), T4, and T5 (monitoring 10 and 20 min after T3). Secondary outcomes are respiratory mechanics and hemodynamic parameters.

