## Introduction

Neurocritical patients with acute neurological impairment, especially stroke, often require the use of mechanical ventilation (MV) [1, 2], either by lowering of the level of consciousness (due to lesion in the thalamus, limbic system, reticular formation in the brainstem), protection of the airways (brainstem), or respiratory control (respiratory center in the cortex, bulb, and pons) [3].

Prolonged MV dependence associated with brain-lung crosstalk and immunosuppression induced by ischemic event [2, 4, 5] can increase the retention of lung secretions and lead to pulmonary complications with an underlying higher risk of death [2].

Evidence corroborates the benefits of using strategies for the removal of secretion associated with MV [6, 7], including MHM, which has been widely applied and discussed [8, 9]. However, hyperinflation causes higher intrathoracic pressure (ITP), which can influence cardiac output (CO), mean arterial pressure (MAP), and intracranial pressure (ICP) [10], thus compromising the indication of this technique. Even though some studies have demonstrated cardiovascular stability during MHM [11, 12], no studies have addressed the monitoring of ICP or intracranial compliance (ICC) during and after the maneuver performance in critical neurological patients. This possibly occurs due to the barrier imposed by the invasive method involving skull trepanning and insertion of a catheter in the cranium, required for monitoring the ICP in traditional methods [13]. Although the technique of inserting a cerebral catheter is the gold standard and most recognized measure for ICP monitoring, the exigence of surgical intervention, training, and specific interpretation technique make it financially unviable for studies at intensive care units (ICUs) on a small and large scale.

Over the past few years, a new instrument has been proposed for non-invasive monitoring of ICC through a sensor capable to detect bone cranial deformation derived from ICP variation [14, 15], which allowed to monitor these patients, called Brain4care (B4C) sensor. The method is in good agreement with the invasive method, the gold standard for the detection of intracranial hypertension [16].

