**Fig. 2 Fig2:**
[figure not shown]
Schematic drawing of experimental design. T0 to T5 represents the assessment stages. DD, dorsal decubitus; EG, experimental group; MHM, mechanical hyperinflation maneuver; CG, control group

Assessments will range five stages: T0 (monitoring start), T1 (before ventilation maneuver for the intervention or control groups), T2 (end of ventilation maneuver our control), T3 (after tracheal aspiration), and T4/T5 (monitoring after 10 and 20 min of procedure). The five initial minutes are required for the initial collection of hemodynamic, ventilation, and neurological data. After the start of this period is T1 with a 10-min duration, followed by T2 and T3, with a 5-min duration each. The individuals in T1 who constituted the MHM group will have their ventilation parameters altered for 10 min according to the lung hyperinflation maneuver adopted, subsequently returning to the baseline values. During this period, the individuals in the control group will be only monitored. In T2, both groups will be subjected to tracheal aspiration; subsequently, data will be monitored for 5 min. Finally, the individuals of both groups were monitored at T4 and T5, 10 and 20 min after the procedure, respectively, to verify vital data stabilization (Fig. 2).

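### The key time T2 lies at or after the end of the maneuver and no assessment is defined as during it, so equivalence at T2 alone cannot show that the maneuver leaves intracranial compliance unchanged

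*Protocol article*

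**What the plan says.** **Key time.** The section on intracranial compliance says: "The moment of evaluation T2 is the most relevant for the primary outcome". The Abstract defines it as "T2 (moment after the MHM and before tracheal aspiration"; the text under Fig. 2 has "T2 (end of ventilation maneuver our control".

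**T1.** The Abstract has "T1 (moment before MHM" and the section on intracranial compliance has "T1: capture initial patient data". The text under Fig. 2, however, makes T1 a 10-minute period and says that the hyperinflation group has its ventilator settings altered in T1 for 10 minutes, "subsequently returning to the baseline values". The Control group section puts the matching control period between T1 and T2.

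**Rationale and claim.** The Introduction names higher intrathoracic pressure as the route to a change in intracranial pressure and says that "no studies have addressed the monitoring of ICP or intracranial compliance (ICC) during and after the maneuver performance" in these patients. The Abstract and the end of the Discussion expect to show that the maneuver is safe; the Abstract adds that compliance does not change.

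**Data.** Non-invasive intracranial pressure "will also be monitored during all procedures and 20 min after the end of the collections" (Safety assessment), and the waveform is processed as one-minute averages (Intracranial compliance). Statistical methods plans a two-way repeated-measures ANOVA over five times.

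**The concern.** The suspected harm is driven by pressure and, on the Discussion's own account of physiotherapy techniques, transitory. The decisive comparison is nevertheless placed at or after the end of the exposure. In an equivalence trial this errs in the favorable direction: if a change fades before T2, the groups move together and equivalence becomes easier to declare.

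The two descriptions of T1 add a second problem. If the maneuver is delivered inside T1 and T1 also serves as the baseline, an effect during exposure becomes part of the reference against which T2 is read. At stake is the trial's headline statement that the maneuver does not change compliance.

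**Working it through.** **Step 1. Where the 10 hyperinflation minutes fall.** The article supports two timelines.

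| Source | T1 | Maneuver | T2 | Hyperinflation minutes in T1 | Hyperinflation minutes in T2 |
|---|---|---|---|---|---|
| Abstract, Control group, Intracranial compliance | moment before | between T1 and T2 | moment after | 0 of 10 | 0 of 10 |
| Text under Fig. 2 (5 min initial, then 10, 5, 5) | minutes 5–15 | minutes 5–15 | minutes 15–20 | 10 of 10 | 0 of 10 |

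On the first timeline no analysed time contains exposure. On the second all of it sits in T1. Neither compares the exposure period with a pre-exposure baseline.

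**Step 2. Is T2 free of the exposure?** The passages disagree.
- The text under Fig. 2 places the return of settings directly after the 10 minutes.
- The Experimental group section says the settings are held for 10 minutes, but mentions readjustment to the initial parameters only after aspiration.
- Table 1 marks the intervention at T2 and T3 in both groups.
- Aspiration falls in T2 under Fig. 2, in T3 in the Control group section, and after T2 in the Abstract.

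**Step 3. How much of a transient change could T2 retain?** The article gives no decay rate, so this only illustrates. Assume that settings are restored at the start of T2 and that the change decays with half-life h minutes. The mean fraction retained over a window of w minutes is

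R = h × (1 − 2^(−w/h)) / (w × ln 2).

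| h (assumed) | w = 5 (T2 as a 5-minute mean) | w = 1 (first-minute reading) |
|---|---|---|
| 1 min | (1 − 2^−5)/(5 ln 2) = 0.28 | (1 − 2^−1)/ln 2 = 0.72 |
| 2 min | 2(1 − 2^−2.5)/(5 ln 2) = 0.48 | 2(1 − 2^−0.5)/ln 2 = 0.85 |

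A true change of 1.0 SD during the maneuver would appear at T2 as 0.28 to 0.48 SD, or as 0.72 to 0.85 SD. With h = 5 and w = 5, R = 5(1 − 2^−1)/(5 ln 2) = 0.72.

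**Step 4. If T1 is the maneuver window.** With a mean change of 1.0 SD over T1, T2 minus T1 would be R − 1. That is −0.72 to −0.52 SD for the 5-minute mean, and −0.28 to −0.15 SD for the first-minute reading. Recovery from the exposure would then look like a shift in the opposite direction.

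**The case against.** - **Exposure data may be analysed.** A reader might infer that hyperinflation readings never enter the comparison. The document does not support that: under Fig. 2 the maneuver lies inside T1, which is an analysed time. This stands. It does not rescue the plan, because T1 is elsewhere the baseline.
- **T2 may still reflect the exposure.** A reader might also take it as settled that the ventilator is back at baseline by T2. It is not. T2 is also called the end of the maneuver, readjustment is also mentioned only after aspiration, and Table 1 marks the intervention at T2. This stands as an unresolved contradiction.
- **The dilution is undetermined.** The 28% to 48% needs an assumed half-life and a 5-minute T2 mean starting at restoration. The only passage that gives T2 five minutes also puts aspiration in it. Elsewhere T2 is a moment, and a first-minute reading keeps 72% to 85%. This stands.
- **Equivalence at T2 does not prove mere recovery.** It is equally consistent with compliance never having changed. This stands: the point is that T2 cannot tell the two apart.
- **The maneuver is monitored.** Collection is suspended for neurological instability, and details of aggregation may sit in an analysis plan that is not shown. Monitoring is not a group comparison, however, and the article itself fixes which time matters most.

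**Conclusion.** The point holds in a limited form. T2 is at or after the end of the maneuver, no assessment is defined as during it, and T1 has two incompatible descriptions. Hyperinflation minutes therefore enter either no stated comparison or the baseline. Equivalence at T2 alone cannot support a claim of no change in compliance from the maneuver, since a transient change during exposure could be missed.

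The size of the possible loss cannot be determined from the document. Retention of 28% to 85% covers the two assumed half-lives and two readings of T2 in Step 3. It is no estimate, and it presumes settings restored at the start of T2. The gap lies in the defined comparison and not in data capture.

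**What to change.** 1. Reconcile the Abstract, Table 1, the text under Fig. 2, the Experimental group and Control group sections and the section on intracranial compliance, so that the pre-maneuver baseline, the maneuver window and T2 are distinct. State when the settings return and when aspiration occurs relative to T2.
2. Before the data are analysed, pre-specify a between-group comparison of the mean per-minute P2/P1 ratio over the 10 maneuver minutes versus the same 10 minutes in controls. Adjust for a baseline taken strictly before the maneuver; adjusting for T1 as described under Fig. 2 would adjust for the exposure itself.
3. Judge it against a stated equivalence margin. The article gives none that could be reused.
4. Claim no change only if both this comparison and T2 meet the margin. Otherwise limit the conclusion to the period after the maneuver.

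**Cost.** No new measurement and one extra analysis, possibly with more artifact minutes during the maneuver and with a second condition to meet. Recruitment was expected to finish in November 2022 and the article appeared in May 2023, so the change comes late and needs a documented amendment. If that is unwelcome, narrowing the conclusion costs only wording.
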